### Study objectives and endpoints

Table 1 provides a list of the primary, secondary and exploratory outcomes of the study and their associated endpoints and justifications.

### Clinical and laboratory procedures

At screening and enrollment, children and their guardians undergo informed consent and child identify verification (by village chief if child unable to verbalize the name of their guardian). Baseline demographics are collected, including: sex, age, residential address, dengue risk factors (e.g. number of domestic water containers at household, larvicide use), bednet use, past medical history, drug allergies, and any current or previous (within past month) use of over-the-counter, prescription, or traditional remedies. Participants undergo a targeted exam that includes vital signs, height and weight.

At baseline, trained phlebotomists collect 8 ml of peripheral blood in a heparin tube for peripheral blood mononuclear cell processing for future cellular assays and 6 ml in a serum separator tube (SST) for detection of dengue-specific antibodies using the PanBio Indirect IgG ELISA kit. For the serum samples that are found to be positive for DENV IgG, a plaque reduction neutralization test (PRNT) will be performed in order to determine the antibody titer to each of the four DENV serotypes. This will establish a baseline profile for each participant.

At semi-annual follow-ups, participants will undergo venipuncture of 8 ml in a serum separator tube for follow-up dengue antibody assessment *via* ELISA, and for those who have seroconverted to positive since baseline, follow-up PRNT assays will be done. At the first semi-annual follow-up, additional whole blood of up to approximately 2 ml will be taken for alpha-thalassemia typing and point-of-care hemoglobin testing. At the final visit of the study, 8 ml of whole blood in a heparin tube will again be taken for PBMC processing for future cellular assays.

Sick febrile visits may occur at any point during the three years. Upon enrollment, participants are given a thermometer to monitor their temperatures at home, call their Community Engagement liaison if they have a fever, and go to the Pediatrics ward at the referral hospital and present their study identification card to undergo vital signs, a dengue-specific sick questionnaire, targeted exam, and rapid diagnostic dengue test. Per Cambodian National Dengue Treatment Guidelines, all children with symptomatic dengue infection are hospitalized. If a patient is found to screen positive for dengue using the SD Bioline Dengue Duo kit, the participant undergoes the following: (i) Day 0 collection for RT-PCR confirmation of arboviral diagnosis, sera for *Ae. aegypti* SGH ELISA and dengue IgM dengue IgM/IgG ELISA, and PBMCs; (ii) Day 7 collection of 5 ml in SST for paired sera between acute and convalescent samples to detect IgM seroconversion or 4-fold increase in total anti-DENV antibodies as measured by ELISA; and (iii) Day 28 collection for 5 ml in SST for sera and 8 ml in heparinized tube for PBMCs for cellular assays. Complete blood counts are already performed as part of the hospitalization per national treatment guidelines, and this information is captured in the patient’s clinical research form (CRF). If the result of the dengue rapid test is negative, the physician will manage the participant as a non-dengue case and advise them accordingly. If the doctor still strongly suspects dengue despite negative rapid testing, or he/she suspects CHIKV or ZIKV infection, the study physician may request collection of 1 ml of whole blood in an EDTA tube to undergo Fast Track Diagnostics® RT-PCR multiplex testing for the viruses in the central CNM-NIH laboratory in Phnom Penh. Of note, no additional phlebotomy for research purposes at sick visits will be performed if a child just underwent venipuncture at a scheduled visit within the preceding 14 days.

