## Methods/Design

### Study design and objectives

This is a prospective pagoda (community)-based cohort study with the following primary objectives: (i) to determine the seroprevalence of antibodies indicating previous *Aedes*-transmitted DENV infection in children; and (ii) to describe the seropositivity to *Aedes* salivary gland homogenate (Table 1). The study will screen up to 1200 and recruit up to 771 children aged 2–9 years for study enrollment and then follow them longitudinally for three years. The study is being conducted over three years given the high rate of variability in *Aedes*-transmitted disease transmission from year to year. The study is focused on children aged 2–9 years of age as they have the greatest burden of disease in Cambodia and thus offers comparability to other pediatric DENV cohorts [23–25, 27].

**Table 1 Tab1:** Study objectives and endpoints

Objectives	Endpoints	Justification for endpoints
• Primary		
Describe the seroprevalence of dengue infection (both symptomatic and inapparent) in children aged 2–9 years-old in Kampong Speu	Prevalence of symptomatic and inapparent dengue infection (serotypes 1–4) as detected semiannually *via* ELISA (binary outcome present/absent) over a 3-year period in Kampong Speu in children aged 2–9 years-old	Detailed knowledge of dengue seroprevalence and transmission season variability will help establish an epidemiological foundation to prepare for larger future studies such as disease incidence studies or vector interventional trials
Describe the seroprevalence of reactivity to *Ae. aegypti* salivary gland proteins in children aged 2–9 years-old in Kampong Speu	Prevalence of *Ae. aegypti* salivary gland homogenate reactivity as detected by ELISA assay (binary outcome present/absent) during wet and dry seasons over a 3-year period in Kampong Speu in children aged 2–9 years-old	Characterizing the *Ae. aegypti* salivary protein reactivity profile in Cambodians is the first step prior to assessing how *Ae. aegypti* saliva exposure modulates disease in humans
• Secondary		

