### Sample size calculation

There are no published seroprevalence studies exclusively for Cambodian children, but multiple pediatric seroprevalence studies are reported from neighboring Thailand and Malaysia [29–31]. The most recent incidence studies in Cambodia suggest that the most conservative estimate, or the lowest incidence rate, of acute dengue infection in Cambodia as approximately 14 per 1000 person-seasons (range 13.7–58 per 1000 person-seasons in neighboring province to Kampong Speu) [24].

It is difficult to make presumptions regarding the exposed mosquito saliva protein (MSP+) and unexposed mosquito saliva protein (MSP-) populations as the only available retrospective study data from Thailand suggested that seroconversion occurs to major *Ae. aegypti* proteins 0–25% of the time in non-infected hospitalized children *versus* 0–75% in DENV-infected hospitalized children [19]. Therefore, the sample size was primarily determined by the number necessary for DENV seroprevalence. With a sample size of 701 accounting for 10% dropout to yield a total goal enrollment of 771 participants, a simple random sample of a binary response (infected or not) with an exact 95% confidence interval on the true proportion will have an average length of less than or equal to 0.075 regardless of the true rate.

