### Statistical analysis

The primary endpoints will be defined as:(i)Seropositivity to DENV1-4 per indirect IgG ELISA (with plaque reduction neutralization assays performed as necessary to confirm inapparent dengue infections)(ii)Seropositivity to *Ae. aegypti* salivary gland homogenate

Seroprevalence to each dengue serotype will be presented as a proportion for each timepoint. Unadjusted and adjusted logistic regression models will be performed evaluating the relationship between time and seroprevalence, with adjustments for age, year or season of collection, and socio-economic conditions (e.g. type of housing). Further, the seroconversion rate and change in the immune status will be determined by participants and separated by age group during the study period. Quasi-Poisson regression models will be fit to evaluate the relationship of age, year, socio-economic conditions (e.g. type of housing) to the primary endpoints of dengue infection or *Ae. aegypti* salivary gland homogenate seropositivity and to estimate prevalence ratios.

Because seroconversion to *Ae. aegypti* salivary gland homogenate is measured repeatedly on subjects over three years during wet and dry season, a single subject may be negative for seroconversion at one time, and positive at a later time. This will allow us to perform our secondary objective to evaluate the kinetics of the antibody response. Given these changing values, seroprevalence to *Ae. aegypti* salivary gland homogenate will be presented as proportion representing point prevalence for each season in each year of the study.

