While one strength of the study is its prospective design to limit selection bias, the study is not powered to define acute dengue incidence, which would number children in the thousands. Therefore, in correlating with mosquito saliva antibody reactivity, the endpoints include both inapparent and symptomatic dengue cases. Further, the study is limited to children aged 2–9 years of age as this is the age strata at greatest risk of dengue. However, neighboring Thailand and Malaysia have recently witnessed a shift in age such that young adults (aged 16–25 years) are now at greatest risk of dengue infection [29, 31]. This study will be unable to comment on whether Cambodia is undergoing a similar demographic shift. Given the presence of multiple circulating flaviviruses in the region and an ongoing JEV vaccination campaign [51], it is possible that cross-reactivity between flaviviruses will cause false positivity on the dengue antibody ELISA assays. Dengue PRNT assays will be performed in order minimize the problem and will provide an important epidemiological assessment of asymptomatic or unreported dengue infections. Lastly, given the limitations of translating preclinical findings in animal models with controlled and known biting exposure to real-life human populations, the observed MSP reactivity patterns in this cohort study may not reflect actual human-mosquito contact as previous studies have shown some heterogeneity with regard to disease outcomes [17, 19, 52]. The frequency of exposure to mosquito bites of the cohort participants during the study is unmonitored and it may be a factor in influencing differences in MSP reactivity and dengue infection severity. For these reasons, well-characterized sera controls will be used in the ELISA assays as well as incorporating extensive demographic data, behavioral activities and disease incidence of apparent and inapparent dengue infections into statistical models.

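### Follow-up PRNT is limited to new seroconverters, so inapparent later infections in children IgG-positive at baseline are not routinely detected, and serotype-specific seroprevalence at follow-up visits is incomplete and biased low

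*Protocol article*

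**What the plan says.** Clinical and laboratory procedures sets two PRNT rules. At baseline: "For the serum samples that are found to be positive for DENV IgG, a plaque reduction neutralization test (PRNT) will be performed", giving a titre to each of the four serotypes. At the semi-annual visits every child has an ELISA, but "for those who have seroconverted to positive since baseline, follow-up PRNT assays will be done". The ELISA is an indirect IgG kit, and Table 1 makes its result binary.

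Three other places ask for more than these rules deliver:

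- Table 1, first primary endpoint: "Prevalence of symptomatic and inapparent dengue infection (serotypes 1–4) as detected semiannually".
- Statistical analysis: "Seroprevalence to each dengue serotype will be presented as a proportion for each timepoint".
- Discussion, on relating infection to saliva antibody: "the endpoints include both inapparent and symptomatic dengue cases".

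Two places bear on how wide the gap is. The primary endpoint definition in Statistical analysis adds PRNT, "with plaque reduction neutralization assays performed as necessary to confirm inapparent dengue infections". For febrile children with a positive rapid test, Clinical and laboratory procedures provides RT-PCR and paired sera "to detect IgM seroconversion or 4-fold increase in total anti-DENV antibodies as measured by ELISA", whatever the child's baseline serostatus.

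**The concern.** PRNT is the only serotype-specific antibody assay described. The follow-up trigger is a change from negative to positive, which a child positive at baseline cannot show while remaining positive. Two promised results are affected:

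- **Serotype proportions after baseline.** For baseline-positive children these can only be old values carried forward, or missing.
- **Counts of new inapparent infection.** These become, without saying so, counts of first infections in seronegative children. If baseline-positive children stay in the denominator, for instance in the exploratory model of infection on saliva seroconversion, their undetected infections are recorded as non-infections. That model refers to subjects at risk, but the article does not say whether this excludes them.

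**Working it through.** **The plan's own figure.** The only design figure is the sample size. With exact (Clopper-Pearson) 95% intervals the average length at n = 701 is largest at a true rate of 0.5, where it is 0.0753, or 0.075 to the precision stated (706 is the smallest n at or below 0.0750). 701 × 1.10 = 771.1 gives the 771. The figure reproduces. It concerns a binary ELISA proportion and does not depend on the PRNT rule.

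**Step 1: trace an inapparent infection through the assay rules.**

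| Child at baseline | PRNT at baseline | ELISA after an inapparent infection | PRNT at follow-up |
|---|---|---|---|
| IgG-negative | none | negative to positive | yes |
| IgG-positive | yes, four serotypes | positive to positive, no change | not under the stated rule |

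**Step 2: effect on a serotype proportion.** At a follow-up visit, the children with antibody to a given serotype are A + B + C:

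- A: baseline-positive children who already had it
- B: new seroconverters who have it
- C: baseline-positive children who acquired it after baseline

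The stated rules yield A (carried forward) and B, not C. The reported proportion (A + B)/N is short by C/N. C cannot be negative and accumulates with each season, so the bias is downward and grows. If baseline-positive children are treated as missing instead, the result describes only the initially seronegative children.

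**Step 3: how many children.** N+ = 701 × p, where p is baseline IgG prevalence. The protocol gives no p, so a range of 10% to 70% is assumed.

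**Step 4: illustrative new infections in them.** Expected number = 701 × p × [1 − (1 − r)^S]. For r, Sample size calculation takes about 14 as its conservative value and gives a "range 13.7–58 per 1000 person-seasons in neighboring province to Kampong Speu". S, the number of seasons at risk in three years, is assumed to be 3 to 6. The same risk is assumed whatever the baseline serostatus.

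- Low: 1 − 0.986^3 = 0.041
- High: 1 − 0.942^6 = 0.301

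| Assumed p | Children without routine follow-up PRNT | New infections among them, low to high |
|---|---|---|
| 10% | 70 | 3 to 21 |
| 30% | 210 | 9 to 63 |
| 50% | 351 | 15 to 106 |
| 70% | 491 | 20 to 148 |

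At p = 30%, 8.7/701 = 1.2 and 63.4/701 = 9.0 percentage points. If each infection adds one serotype, that is the shortfall summed over the four serotypes by the end of follow-up.

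These counts show order of magnitude only. The cited rates are for acute dengue. Symptomatic cases may be caught at sick visits, while inapparent infections would come on top of the cited rates.

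**The case against.** **Febrile visits.** A reader might infer that every later infection in a baseline-positive child is invisible. The document does not support that. A febrile child of any serostatus gets a rapid test and, if it is positive, RT-PCR and paired sera. RT-PCR can also be requested on clinical suspicion after a negative rapid test. This stands and confines the gap to inapparent infections. Whether the RT-PCR identifies the serotype is not stated.

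**PRNT as necessary.** The Statistical analysis wording leaves room for further PRNT, and the section also mentions change in immune status. But it gives no rule for baseline-positive children, and the binary ELISA gives no signal in them that would prompt a confirmatory test.

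**The primary endpoint.** A reader might infer that the primary endpoint or the sample size fails. Neither does, as far as the endpoint is binary ELISA seropositivity. A child positive at baseline is correctly counted positive later, and a second infection does not change that proportion.

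**Level of detail.** A condensed article may leave the laboratory algorithm to the full protocol. That would excuse silence. Here the article states both a restrictive rule and an output the rule cannot fully supply.

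**A percentage missed.** It is tempting to state that some fixed share of new infections is lost. With equal risk in both groups, the share arising in baseline-positive children equals the assumed baseline prevalence by construction, and it includes symptomatic cases that can be caught. It is no independent evidence of size.

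**Conclusion.** The point holds in a limited form. As written, children IgG-positive at baseline get no routine PRNT at follow-up. Inapparent later infections in them are not routinely detected, and serotype-specific seroprevalence after baseline is incomplete and biased low.

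It would be too strong to say that serotype-specific seroprevalence cannot be produced. It can be at baseline, where every IgG-positive serum is tested, and new seroconverters are typed at follow-up. Bias in the saliva-infection relative risk is possible but not shown. It depends on whether baseline-positive children stay in the denominator and on how their saliva status differs.

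The size rests on an assumption: with 10% to 70% baseline-positive, about 70 to 491 of 701 children are affected. The infection counts rest further on the cited incidence range, 3 to 6 seasons and equal risk by serostatus.

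**What to change.** Reconcile Clinical and laboratory procedures with Statistical analysis.

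1. **Serotype output.** Report serotype-specific seroprevalence for the whole cohort at baseline only. At follow-up, report serotype results for new seroconverters only, labelled as such. This keeps all PRNT results the plan generates.
2. **Infection events.** Keep binary ELISA seroprevalence at all visits as planned. In analyses of new inapparent infection, including the exploratory saliva-infection model, restrict ELISA-defined events and their denominator to children seronegative at the previous visit. Analyse symptomatic RT-PCR-confirmed infections in all children.

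Both changes are wording and analysis definitions, at almost no cost.

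Optional, at a laboratory cost, using stored sera:

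- **PRNT at the final visit in baseline-positive children**, compared with baseline. This needs about 70 to 491 further sera on the assumed range before dropout, or twice that if baseline sera are re-run alongside. It restores whole-cohort serotype prevalence at the end of the study but does not date the infections.
- **PRNT on consecutive pairs flagged by a prespecified ELISA rise.** Baseline plus six visits gives six pairs per child, so 70.1 × 6 = 421 to 490.7 × 6 = 2,944 pairs must be read side by side. If 5% are falsely flagged (an assumption), that adds about 21 to 147 PRNT pairs to the true rises. The Discussion itself warns of flavivirus cross-reactivity and an ongoing Japanese encephalitis vaccination campaign, so false flags should be budgeted for.

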### Data collection, monitoring, and storage of research samples

Upon enrollment in the protocol, all subjects will be assigned a unique identifying combination code of seven numbers (e.g. 100-0001). The identifier will serve to link this identifying code with subject name. CRFs, databases, and biological samples including DNA will be coded with unique identifying numbers and will not contain subject names. Study personnel involved in data acquisition, entry, and analysis will therefore not have access to names, assuring the privacy and confidentiality of subjects.

REDCap (Research Electronic Data Capture) serves as the core data collection component of the data management system hosted at NIAID. REDCap is a secure, web-based application designed to support data capture for research studies, providing: (i) an intuitive interface for validated data entry; (ii) audit trails for tracking data manipulation and export procedures; (iii) automated export procedures for seamless data downloads to common statistical packages; and (iv) procedures for importing data from external sources [32]. Standard CRFs containing clinical and laboratory data will be completed on iPads using the REDCap that will be locked with a code and uploaded to password-protected servers. Relevant subject data will be entered into a hybrid system (REDCap plus Datafax©). Electronically captured data will be checked by study investigators and verified by a data manager. All electronic data will be stored on a secure server.

Following written standard operating procedures (SOPs), external study monitors will verify that the clinical trial is conducted, data are generated, and biological specimens are collected, documented (recorded), and reported in compliance with the protocol, good clinical practices, and applicable regulatory requirements.

The PI will retain all study records for at least 5 years in compliance with institutional, institutional review board (IRB), state, and federal medical records retention requirements, whichever is longest. Data captured electronically *via* tablets will be backed up nightly to the site’s central server and transmitted on a weekly basis. All data will be archived at the end of the study and retained for a period of time consistent with IRB requirements.

All human biological samples will be received, processed, aliquoted, and stored at the central CNM laboratory in Phnom Penh according to standard laboratory procedures.

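### No pre-conversion serum is scheduled for PRNT or parallel re-testing, so a past infection missed by the baseline ELISA can later be confirmed as a new inapparent infection

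*Protocol article*

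**What the plan says.** The protocol article, Clinical and laboratory procedures, gives two triggers for PRNT:

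- At baseline: "For the serum samples that are found to be positive for DENV IgG, a plaque reduction neutralization test (PRNT) will be performed". The article adds: "This will establish a baseline profile for each participant".
- At the semi-annual visits: "for those who have seroconverted to positive since baseline, follow-up PRNT assays will be done".

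Statistical analysis defines the dengue primary endpoint as seropositivity on the indirect IgG ELISA, "with plaque reduction neutralization assays performed as necessary to confirm inapparent dengue infections". The same section promises a seroconversion rate by age group.

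The Discussion gives the reason for PRNT. Because of other flaviviruses and a JEV vaccination campaign, "it is possible that cross-reactivity between flaviviruses will cause false positivity on the dengue antibody ELISA assays". It does not mention ELISA false negatives.

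For febrile children who screen positive on the rapid test, the plan uses RT-PCR and also pairs sera: "Day 7 collection of 5 ml in SST for paired sera between acute and convalescent samples to detect IgM seroconversion", or a fourfold rise in total antibody by ELISA. On storage, the article says: "All human biological samples will be received, processed, aliquoted, and stored".

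**The concern.** A new inapparent infection is recognised by an ELISA that is negative at baseline and positive later, with PRNT as the confirming test. PRNT on the later serum guards against one error: a positive ELISA caused by another flavivirus. It does not guard against a negative baseline ELISA in a child who already had dengue antibody. If that child later crosses the cut-off through assay variation, or through a boost from another flavivirus or JEV vaccination, PRNT will tend to be positive because the dengue antibody is real.

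Two outputs are at stake:

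- **Seroconversion rate by age group.** Cumulative past infection rises with age, so any old infections counted as new would fall more on the older age bands.
- **Exploratory saliva-infection analyses.** The Discussion says the endpoints for correlation with saliva reactivity include inapparent as well as symptomatic dengue. It also treats saliva antibody as a marker of exposure to the vector. Past infection and saliva reactivity may therefore go together, and the error need not be equal in the groups compared.

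**Working it through.** **Step 1. The two triggers side by side.**

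| Child | Baseline ELISA | Baseline PRNT scheduled? | Follow-up ELISA | Follow-up PRNT scheduled? |
|---|---|---|---|---|
| Already positive | positive | yes | any | no trigger stated |
| Stays negative | negative | no | negative | no |
| Seroconverter | negative | no | positive | yes |

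The seroconverter row is where new infection is counted, and in that row PRNT is scheduled on the later serum alone. The statement about a baseline profile for each participant does not hold for these children as far as PRNT is concerned.

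**Step 2. Size.** The plan gives no figure on this point, so there is none to reproduce. ELISA sensitivity, baseline prevalence and the fraction of missed children who later cross the cut-off are not in the document and are assumed. The total infection rate is also assumed, because the rates quoted in the article (41 per 1000 person-seasons in Background; about 14, range 13.7 to 58, in Sample size calculation) come from case surveillance, and the latter are labelled acute infection.

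Inputs: N = 771 (enrolment goal); prevalence p = 0.40; sensitivity s = 0.90, 0.95, 0.98; total infection rate i = 0.10 per season over three seasons; crossing fraction r = 1 or 0.5.

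- Missed at baseline = N × p × (1 − s)
- True new infections = N × (1 − p) × (1 − (1 − i)³) = 771 × 0.60 × (1 − 0.729) = 462.6 × 0.271 = 125.4
- False share = r × missed / (r × missed + true new)

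| Sensitivity | Missed at baseline | False share, all cross | False share, half cross |
|---|---|---|---|
| 90% | 771 × 0.40 × 0.10 = 30.8 | 30.8/156.2 = 20% | 15.4/140.8 = 11% |
| 95% | 771 × 0.40 × 0.05 = 15.4 | 15.4/140.8 = 11% | 7.7/133.1 = 6% |
| 98% | 771 × 0.40 × 0.02 = 6.2 | 6.2/131.5 = 5% | 3.1/128.4 = 2% |

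N cancels from the share, so using 701 instead of 771 changes nothing. The calculation takes every new infection as detected. If the ELISA missed new infections at the same rate as old ones, the 90% row with all crossing becomes 30.8/(30.8 + 0.90 × 125.4) = 21%.

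**Step 3. How far the assumptions move the result.** A grid with N = 701, prevalence 10 to 50%, sensitivity 85 to 99%, crossing 25 to 100%, the article's 14 to 58 per 1000 per season, and new infections detected with the same sensitivity gives false shares from under 1% to about 81%. The upper end uses an acute-case rate as if it were all infections, which makes the true count too small. The grid shows that the size is not known.

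**The case against.** The strongest reply is that newness comes from the change between two ELISA results, not from a single PRNT, and that PRNT is there only for specificity. This is a condensed article. It does not say that follow-up serum alone may be tested, its wording on PRNT in Statistical analysis leaves room for paired testing, and the sera are kept. All of that stands. A reader might infer that the protocol rules out re-testing an earlier serum. The text supports only that no such test is scheduled under the stated triggers.

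Three other stronger readings are not supported:

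- **That every missed child will be counted as new.** This happens only if the child crosses the cut-off without a new dengue infection. Table 2 lists six follow-up sera, but they are not six independent chances: stable low antibody may stay below the cut-off throughout. A missed child who crosses because of a real new infection is counted correctly.
- **That the false share is 36/22/10%.** These values come from the same formula at 40% prevalence with 41 per 1000 per season: true new = 462.6 × (1 − 0.959³) = 54.6, and 30.8/85.4 = 36%. But 41 per 1000 is a case rate in children under 7, not total infection, and the figure also takes all missed children to cross. It fits poorly with 40% prevalence: at constant transmission and a mean age of about 6 years (assumed), 40% implies −ln(0.6)/6 = 8.5% per year. That gives 462.6 × (1 − 0.6^0.5) = 104 new infections and shares of about 23/13/6% with all crossing.
- **That the primary seroprevalence is inflated, or that inapparent infections are most of the events.** A past infection detected late is truly seropositive, so this mechanism adds no false positive to point prevalence. The article says only that both kinds of infection are included.

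What the reply does not answer is that an ELISA pair read at different visits cannot separate a missed past infection from a new one, and that the confirming test as scheduled cannot either.

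**Conclusion.** The point holds in a limited form. Under the stated triggers, no seroconverter's pre-conversion serum is scheduled for PRNT or for parallel re-testing, so an old infection missed at baseline can be confirmed as a new inapparent one. The consequence is confined to the seroconversion rate by age and to the exploratory saliva-infection analyses. Point seroprevalence, RT-PCR-confirmed cases and the sample size are not affected.

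The size is unknown. Under the illustrative set (40% prevalence, 100 infections per 1000 per season, all new infections detected), the share is about 20/11/5% at 90/95/98% sensitivity if all missed children cross, and about 11/6/2% if half cross. It would be negligible with a highly sensitive ELISA or little crossing. As scheduled, the testing would not show which case applies. This is a worthwhile, inexpensive improvement, not a flaw in the primary estimates.

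**What to change.** Add to Clinical and laboratory procedures that, for each seroconverter, the stored last-negative serum is run beside the first-positive serum in the same ELISA run and the same PRNT run. Add to Statistical analysis that a new inapparent infection is counted only if the last-negative serum is confirmed negative or a minimum rise between the two sera, set in advance, is seen. The rise criterion keeps children with missed past infection who then have a real new one. This brings inapparent infections closer to the paired comparison already used for febrile cases.

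The cost is one extra stored-serum assay per converter and no new blood draw. In the illustration with all missed children crossing, that is about 132 to 156 children (125.4 + 6.2 to 125.4 + 30.8), and fewer at lower incidence. The work can be batched. The downside is that a few true converters with a low rise will not be counted; reporting how many fail the rule would show the size of both errors.
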